**Figure 1 figure1:**
[figure not shown]
Study design of the LINX study.

### Mobile App Development

In phase 1, we conducted qualitative interviews with BSMM+ in LAC focused on technology use patterns, HIV diagnosis and engagement in care, and social and legal service needs. Using these data, we worked with a private sector technology partner, Philosophie Group Inc [20], to engage in an iterative, user-centered design process to develop the LINX App. Throughout the intensive 6-week design process, we developed an interactive prototype and conducted moderated interviews with BSMM+ (n=20) and HIV service providers (n=11). Participants tested the functionality of a paper prototype of the LINX App through moderated interviews and to evaluate the prototype according to user experience principles (eg, content and delivery of content is useful, findable, accessible, desirable, usable, and credible). The phase 1 design process ended with a 1-week pilot test of the LINX App with BSMM (n=14), including members of the LINX LA Study Community Advisory Board (CAB).

Study staff developed a library of content including over 1000 informational posts in areas of need identified during phase 1 and issues raised during moderated interviews. The 6 main categories include health, fun, legal, relationships, services, and housing with a focus on sharing information related to HIV knowledge, HIV-related services in the community, legal rights and resources available to people living with HIV, and social services and programs. Users can also create their own content on the app, including both creative and informational posts. With the ability to post photos and videos using YouTube and Vimeo platforms, posts have the potential to be dynamic and engaging. Examples of the app interface with mockup text are shown in Figure 2.

**Figure 2 figure2:**
[figure not shown]
LINX App user interface.

### Recruitment

Recruitment strategies will include the following efforts (Textbox 1).

Recruitment strategies.Meetings with key stakeholdersAttend in-person meetings with key collaborators in the community including Public Health Departments, community clinics, Los Angeles County (LAC) HIV Commission, and other health care and social service providers serving Black sexual minority men (BSMM) in LACCommunity partners, stakeholders, researchers, and staff will test and review the mobile app live and distribute study materials to their networksDue to the COVID-19 pandemic, our meetings will be held on the internet using the Zoom Video Communications platformIn-app referral programLINX LA has a built-in referral function to allow participants to refer people directly from the appOnce a referral is made, LINX staff will be notified to follow upParticipants will receive a US $20 Amazon e-gift card for every person successfully referred into the studyReferral programNoninvestigator health care, social and other service providers, and community members will be able to refer others into the studyReferrers are sent a referral code, information about the study, a suggested pitch they can use to talk about the study, and a digital referral card to post on the internetReferrers will receive a US $20 Amazon e-gift card for every person successfully referred into the studyIn-person outreach eventsStaff will distribute flyers and business cards for the study at locations including community events tailored to attracting BSMM, clinics and health centers, bars and clubs, retail businesses, community forums, social service organizations, and other community-based service providersOwing to the COVID-19 pandemic, all in-person outreach events will be put on hold; instead, all outreach will be conducted via phone, social media, and emailWeb-based promotionParticipants will be recruited through web-based methods using targeted advertising on social networking sites (eg, Facebook.com, Twitter.com, SCRUFF.com, Grindr.com, Craigslist.org, Jack’d [Jackd.com], Bareback Real Time Sex [BarebackRT.com], Black Gay Chat Live [BGCLive.com]) in addition to direct email campaignsStaff will engage social media influencers, people with a large number of social media followers, to help widen the reach of our web-based promotion

### Community Engagement

During phase 2 of the LINX study, researchers and study staff will engage in a range of collaborative activities to ensure that research activities are responsive to and understand community needs, views, and expectations.

#### APLA Health: Community-Based Program Implementation

The LINX study will strategically subcontract with APLA Health, a social service organization with over 35 years of work serving LA communities affected by HIV/AIDS, to implement the LINX LA study’s coaching activities. The LINX Coach will be hired from within the community and trained by and embedded within APLA Health’s well-established outreach, prevention, and social services department to ensure cross-training and resource sharing between researchers and community partners. This collaboration will enable underresourced participants to access APLA Health’s full range of in-house wraparound services—social support groups, housing navigation, mental health, benefits counseling, and health care services. APLA Health provides essential services, so their full range of services is still available (albeit some services are limited to specific locations) during the COVID-19 pandemic.

#### Arming Minorities Against Addiction and Disease Institute: Community-Driven Capacity Building and Social Events

The research team will partner with the Arming Minorities Against Addiction and Disease (AMAAD) Institute, a social services organization serving lesbian, gay, bisexual, transgender, and queer (LGBTQ) people of color in South Los Angeles. Since 2014, AMAAD developed a community-driven project to empower young LGBTQ African American people to share personal experiences and life skills through art. This partnership will accomplish several goals: (1) generate culturally appropriate content for the LINX App; (2) create and sustain social support to address isolation and disconnectedness among BSMM+; (3) identify and train BSMM+ *study ambassadors* to talk about the study and recruit peers into the study; and (4) build individuals’ capacity in editorial writing and content creation. During the ongoing COVID-19 pandemic, many AMAAD Institute programs and services, such as support groups, capacity building workshops, and training, have moved to a web-based conferencing platform (ie, Zoom Video Communications Inc).

#### CAB: Input and Feedback

The LINX CAB, made up of community members, community organization partners, and social service providers, will be established at study inception and meet on a quarterly basis to provide feedback and input on study materials, procedures, recruitment strategies, receive updates about the study, and solve implementation challenges. CAB members primarily include BSMM, including individuals living with HIV. During the COVID-19 pandemic, CAB meetings will be held on the internet via the Zoom Video Communications conferencing platform.

#### Community Outreach and Engagement: Resource Gathering and Recruitment

LINX researchers and study staff, which include community members with substantial community organizing and networking experience engaged in the LINX phase 1 formative work, will make efforts to engage with community-based organizations, clinics and health centers, HIV service providers, stakeholders, and community venues that serve or represent LGBTQ African American people across LAC. Activities will include resource sharing and cross-promoting programs and services via LINX LA–branded social media. By regularly attending resource fairs, provider network meetings, and other community meetings, LINX LA study staff will access up-to-date information on social service programs, which will facilitate effective linkages for LINX LA study participants. During the ongoing COVID-19 pandemic, in-person attendance of resource fairs and meetings have transitioned to web-based conferencing platforms.

#### Online Community Engagement: A Social Networking Extension of LINX

The LINX LA study team developed and maintained several LINX LA–branded social media accounts on platforms (eg, Twitter, Facebook, Tumblr, and Instagram) that are popular with users that match the study’s target demographic. The LINX LA study’s presence on social media serves to add to and amplify Black queer voices in the media and in the community and, in doing so, will assist the research project by providing another accessible online space for LINX App and non–LINX App users to engage followers interested in LINX LA’s curated feed who may also be interested in the LINX LA study. Growing a social media following that allows LINX LA to reach more users via followers’ networks goes beyond what is possible with traditional recruitment methods.

Words used to describe the LINX LA social media brand, developed in consultation with the LINX LA CAB, include *young, hip, Black, queer, empowering*, and *positive*, and LINX LA features original and shared content that reflects those themes and messages. Content will include posts about Black queer voices in popular culture, inspirational quotes, monthly themes, community resources, upcoming events, music playlists and videos, and articles about Black queer experiences and experiences of people living with HIV. To enhance reach and effectiveness, the LINX staff will use social media best practices, and analytics will be used to assess the effectiveness of various strategies.

### Enrollment Process

To see if an individual is eligible to enroll, potential participants must first complete a screening that can occur via email, in-person, by phone, or on the web. During the screening, LINX LA study staff will collect information regarding name or alias, age, gender identity, sexual orientation, HIV status, and race and ethnicity. The study staff then schedules in-person enrollment appointments via the participant’s preferred mode of contact. During enrollment, participants are screened for consent and asked to provide additional consent for study staff to access medical records, to provide HIV verification, and to complete a baseline assessment. During the ongoing COVID-19 pandemic, the research staff are not engaging in any in-person activities until the university and the institutional review board (IRB) that oversees the study lift restrictions related to in-person human subjects research. All enrollment activities will be conducted over Zoom Video Communications or by phone.

### Onboarding

After enrollment, participants were assisted by study staff to download the LINX App. Study staff will inform participants of the duration and compensation schedule for the study. Once the app is downloaded, the participant will be instructed how to log into the app and navigate the user interface based on the arm of the study to which the participant is assigned. Participants will be instructed on how to create a post, and the terms and conditions of use will be reviewed in detail.

### Coaching Sessions

Participants are randomly assigned to one of 2 conditions. Those assigned to LINX App Plus have access to a LINX Coach. The LINX Coach delivers 3 manualized intervention sessions via phone calls during the first 6 months of the study (ie, 1 session every other month). These sessions are adapted from a manualized intervention to promote HIV medication adherence developed by Wagner et al [21]—the adherence readiness program.

On the basis of the information, motivation, and behavioral skills model of behavior change, the 3 coaching sessions are conducted over the phone. Using additional counseling techniques based on motivational interviewing, the LINX Coach conducts 3 sessions approximately 2 months apart. Each session includes learning objectives, described in detail below. During these sessions, the LINX Coach helps to identify any social and legal needs the participant may have, provides the participant with social support and needed referrals to legal and social service providers throughout the LAC, and helps motivate participants to identify and pursue their own HIV treatment and adherence goals. The LINX Coach follows-up with participants to ensure that linkages to services have occurred. The LINX Coach also maintains regular contact with participants via 2-way messaging in the LINX App.

In session 1, learning objectives include being able to identify, with LINX Coach support, outstanding social work and legal needs and to discuss HIV treatment engagement issues that the participant may be experiencing. These objectives are achieved by discussing the intervention and expectations of the participants, the participants’ attitudes, beliefs, and goals toward treatment engagement and addressing issues discussed with the LINX Coach that are within the scope of the LINX intervention through linkage to social and legal resources.

In session 2, learning objectives include developing problem-solving skills, where the LINX Coach helps participants apply those skills to the social work and legal needs the participant may be experiencing. The LINX Coach also offers support for the participant to improve and/or maintain continued treatment engagement by addressing issues identified by the participant in session 1. This work is achieved by directly identifying barriers to engagement in care, outlining a strategy for success, and developing strategies to improve social support.

In session 3, the LINX Coach delivers the third and final coaching session. The learning objectives for this session include the participant identifying their own successful strategies for treatment engagement and troubleshooting, with help from the LINX Coach for any remaining social work and legal needs. The participant will design a plan for ongoing treatment engagement. Success in the third session is defined by the participants’ ability to both think and act independently as it relates to the identified social work, legal needs, and treatment engagement issues.

### Weekly Medication Adherence Assessments

Brief text message surveys will be distributed to all study participants to capture weekly medication adherence. The survey comprised 1 to 3 questions asking about adherence in the prior week and, if a participant reports missing their medication, a query about why they may have missed it. Participants who complete the 2-minute survey will earn 1 entry into the monthly raffle for a US $100 e-gift card. Individuals can choose not to participate or to opt out of the survey.

### Incentives

Participants in the LINX App condition will receive up to US $130 in cash, e-gift cards, or web-based cash payment (ie, PayPal Holdings Inc, Venmo LLC, and Cash App by Square Inc). Participants will receive US $30 for the baseline assessment, US $40 for the 6-month posttest interview, and US $60 for attending the 12-month follow-up interview. LINX App Plus participants will receive the same incentives as those in the LINX App condition including additional incentives for each completed coaching session. Participants in the LINX App Plus condition can receive up to US $190 in cash, e-gift cards, or web-based cash payment, as they receive a US $20 incentive per coaching session completed.

#### Discharge From the Study

Participants will be discharged from the study after completing their 12-month follow-up interview. After discharge, all individually identifiable data related to the participants will be destroyed.

### Regulations and Ethics

The research and ethics presented in this study were reviewed and approved by the North Campus IRB of the University of California, Los Angeles (UCLA; IRB#17-001615) with UCLA acting as the IRB on record for all LINX community partners. Additional terms to ensure confidentiality were provided to the participants. These terms include protection for all study-related data obtained by all LINX LA study staff, which includes employees, contractors, volunteers (paid or unpaid), and other professionals staffing the project.

Technical concerns related to data privacy were considered throughout phase I during the app development process. The mobile app is housed by a Health Insurance Portability and Accountability Act–compliant hosting platform often used by health care entities. In collaboration with the UCLA Information Technology and UCLA Compliance departments, considerations related to data storage and data in transit were considered, including the institution’s legal and ethical duties related to the handling of personally identifiable information. User terms for the mobile app were drafted to include specific guidelines on sharing data and personal information and the particular limitations to privacy for individuals who disclose information on the LINX LA app. Users are instructed to select a display name, different from their legal name, and advised not to include full facial photos, phone numbers, and email addresses to protect their identity. Procedures and protocols are established to address participants that may require intervention under the law (eg, participants expressing suicidal ideation) and participants who may be engaging inappropriately on the LINX App.

### Primary Outcomes

The primary outcomes that the study will measure include the degree to which using the LINX App may impact medication adherence and viral suppression. These primary outcomes were assessed through self-reported data verified through an independent medical chart review. The study will measure how outcomes differ between the LINX App and LINX App Plus conditions and whether the intensity of use of the platform (ie, intervention dosage) is associated with these outcomes.

### Secondary Outcomes

The overarching framework that informs the study is a social determinant of health model, where we recognize that structural factors (eg, housing instability and poverty) are upstream factors influencing individual-level health behaviors. The information, motivation, and behavioral skills model is the mechanistic model of behavior change. We posit that in the short term, the LINX App will serve to increase participants’ HIV knowledge and help create connections among the participants and connections to existing community-based resources. This may impact both treatment adherence and address issues related to social isolation and stigma. For participants in the LINX App Plus arm of the study, we hypothesize that by offering social and legal services case management, the study could address 2 primary issues facing many in the target population—housing and financial instability.

### Assessment Measures

The baseline, 6-month, and 12-month surveys comprised 12 topic areas (Table 1).

**Table 1 table1:** Primary and secondary outcomes of the study.

Outcomes		Measures		Variables	
**Primary**					
	Technology use		Multiple items		Likert scale, range 1-5
	Medication adherence		Self-reported medication adherence; HIV medical record data		Dichotomous; Yes or No HIV medication adherence or HIV-associated medical appointment
	Viral supression		Viral load and CD4 counts		Continuous

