## Methods

### Overview

The proposed study is a randomized comparison trial of a web-based mobile app titled *LINX*. Participants will be randomly assigned to either the intervention (ie, treatment group) or the comparison group. Those in the intervention group will receive the app and access to a LINX Coach (*LINX App Plus* condition) and those in the comparison group will receive the LINX Mobile app only (*LINX App* condition). Participants in both arms of the study will remain on the mobile app for 12 months. The overarching goal of the study is to evaluate the efficacy of LINX App Plus compared with LINX App to improve HIV treatment outcomes (ie, ART adherence, viral suppression). The research team did not register this study at ClinicalTrials.gov because it did not involve randomization to a true control group. Owing to ethical concerns about withholding the mHealth intervention, all participants received the app; half were randomized to receive coaching.

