## Discussion

### Limitations: Recruitment Challenges

There are potential challenges to this trial. It employs convenience sampling techniques to recruit the target population, which limits generalizability. In addition, if recruitment fails to yield the required number of participants, we may not have adequate statistical power to detect effects of intervention conditions on outcomes. To address these uncertainties, we plan to compare our sample to data from other projects focused on BSMM+ in LAC. The LAC Division of HIV and STD Programs has implemented a clinic-based medical care coordination (MCC) program to increase viral suppression (VS; <200 c/mL) among people living with HIV at high risk for poor health outcomes (eg, diagnosed with HIV in the past 6 months, on ART without VS, out of care for more than 6 months). The MCC program collects clinical data across 35 Ryan White Program–funded clinics across the county serving these populations, including those that identify with our target population. Comparing results from the study with data from participants in the county’s MCC program will help to address this gap.

Recruitment of BSMM+ may be challenging in LAC due to the sheer size of the county and the study’s eligibility criteria, requiring participants to be both living with HIV and identifying as a sexual minority. For this reason, study staff will implement a diverse set of strategies to engage varied audiences during the recruitment period, including web-based efforts and in-person efforts detailed in Textbox 1. The study will also offer participants with transportation assistance. By providing access to ride-sharing resources through Lyft Concierge services, participants will be able to meet study staff at the location of their choice. This additional support has proven effective in reducing the number of cancelled meetings between study staff and participants [18].

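### Table 1 conflicts with the stated primary outcomes: it adds technology use, codes viral suppression as continuous viral load plus CD4 count, and lets medical appointments stand under adherence

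*Protocol article*

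**What the plan says.** The Overview and Primary Outcomes sections of the protocol article, like the abstract's objective, name two HIV treatment outcomes. Primary Outcomes describes them as "the degree to which using the LINX App may impact medication adherence and viral suppression". The same section gives platform use a different role, asking "whether the intensity of use of the platform (ie, intervention dosage) is associated with these outcomes", so use is an explanatory variable there.

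Table 1, under Assessment Measures, is captioned as the study's primary and secondary outcomes. Its primary block has three rows:

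- "Technology use": multiple items on a 1 to 5 Likert scale.
- Medication adherence, from self-report and medical record data, with the variable given as "Dichotomous; Yes or No HIV medication adherence or HIV-associated medical appointment".
- Viral suppression, measured by "Viral load and CD4 counts", with the variable type given as continuous.

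No threshold for suppression is given for the trial. The only one in the article is in Limitations: Recruitment Challenges, where the county's medical care coordination (MCC) program is described as aiming "to increase viral suppression (VS; <200 c/mL) among people living with HIV".

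**The concern.** These are the primary outcomes, so each mismatch affects what the trial may report as its main result.

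**Viral suppression.** Planned Analytic Approach selects the model by whether the outcome is continuous, categorical or binary. A continuous label therefore points to a linear-type analysis and leaves the proportion suppressed unspecified as the primary test. Adding CD4 count brings in a quantity that does not measure suppression.

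**Adherence.** If an appointment can satisfy the variable, attendance and medication-taking are mixed. The mixing need not be equal between arms. According to Coaching Sessions, only LINX App Plus participants have a coach who makes referrals and checks that linkage to services took place.

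**Technology use.** A third primary outcome that the text does not name adds one more test to those needing multiplicity correction.

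Left unresolved, the text and the table allow different definitions to be chosen after results are seen.

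**Working it through.** **1. Places set side by side**

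| Item | Text of the article | Table 1 |
|---|---|---|
| Number of primary outcomes | Two (abstract, Overview, Primary Outcomes) | Three |
| Platform or technology use | Intervention dosage (Primary Outcomes); usage metrics under Measuring and Maximizing Engagement | Technology use listed as primary |
| Viral suppression | A state that people achieve: 63.3% in California and 52% of African American people living with HIV in LAC (Background); <200 c/mL for the MCC program (Limitations) | Continuous; viral load and CD4 count |
| Adherence | Medication adherence, self-reported and verified by chart review | Medication adherence or an HIV-associated appointment |

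Statistical Analyses names CD4 count and viral load as example outcomes when describing spline checks. That fits the table's label and does not resolve the conflict. The planned comparison with MCC data also needs an outcome on the suppressed/not suppressed scale.

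**2. The plan's own sample-size figure**

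Inputs from Sample Size Calculation and Power Analysis: base rate 70%, difference 12.5 points, α = .05 (taken as two-sided), power 80%, 200 per arm. With p̄ = 0.7625:

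n = [1.96·√(2·0.7625·0.2375) + 0.8416·√(0.70·0.30 + 0.825·0.175)]² / 0.125² = 181 per arm, or 197 with continuity correction.

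The stated 200 is reproduced. It is computed for linkage to care, which is not a primary row of Table 1, and for one test at .05.

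**3. Cost of a third primary test**

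Power at 200 per arm for 70% versus 82.5% is Φ{[0.125·√200 − z·√(2·0.7625·0.2375)] / √(0.70·0.30 + 0.825·0.175)}, with z taken at the Bonferroni level. The last column is the difference detectable with 80% power for a binary suppression outcome, using the article's 52% as an illustrative control rate.

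| Primary tests | α per test | Power, 70% vs 82.5% | Detectable difference from 52% |
|---|---|---|---|
| 1 | .05 | 83.8% | 13.7 points |
| 2 (text) | .025 | 75.9% | 15.1 points |
| 3 (Table 1) | .0167 | 70.9% | 15.8 points |
| 4 (CD4 and viral load tested separately) | .0125 | 67.2% | 16.3 points |

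**4. Illustration of the either/or reading of adherence**

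The rates below are assumptions, not figures from the article. If either event scores yes and the two are independent, P(yes) = 1 − (1 − adherence)(1 − attendance).

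- True adherence 60% vs 70%, attendance 70% in both arms: 1 − 0.4·0.3 = 88% and 1 − 0.3·0.3 = 91%. Ten points become 3.
- Adherence 60% in both arms, attendance 60% vs 75%: 1 − 0.4·0.4 = 84% and 1 − 0.4·0.25 = 90%. An attendance difference shows as a 6-point gain.

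Independence is not essential. Let ρ be the correlation between adherence a and attendance t. Then P(yes) = a + t − [a·t + ρ·√(a(1−a)t(1−t))]. For ρ from 0.3 to 0.5 in both arms, the first difference is about 3.4 to 3.7 points and the second about 7.

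**The case against.** The strongest reply is that Table 1 is partly a survey inventory. It is introduced as the twelve topic areas of the surveys and has twelve rows, some of which, such as sociodemographics and ethnic identity, are plainly not efficacy endpoints. The variables column may record only how data are collected. This has weight, but the caption and the primary and secondary headings present the rows as outcomes, and nothing in the article says otherwise.

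Four stronger readings are tempting and go beyond the document:

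- **That the trial will never test the proportion suppressed, or that a few extreme viral loads would drive the result.** Logistic regression is among the planned methods, and no untransformed linear model is assigned to viral load. Transformation and visit window may be set in a fuller document. What holds is that the proportion is not specified as the primary test.
- **That a non-adherent participant who keeps an appointment certainly scores yes.** The measures cell lists two sources, so the variable could be two separate yes/no items, and Primary Outcomes describes chart review as verification of self-report. Even so, an appointment would still sit under an adherence label.
- **That technology use is LINX uptake, inflated by coach messaging.** App usage is measured separately through logins, time, posts and messages. The Likert items may cover general technology use. On either reading the text does not name it as a primary outcome.
- **That <200 c/mL is the trial's own threshold.** It is stated only for the MCC program.

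The commitment to hold overall type 1 error at .05 also stands. The extra test costs power and does not inflate error.

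**Conclusion.** The conflict between Table 1 and the text is real, and no other section resolves it. As printed, the table adds a primary outcome, gives suppression a continuous label that includes CD4 count, and leaves adherence open to being met by an appointment. It does not show that the trial measures the wrong things: viral load is the right raw measurement, and adherence is collected.

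The firm consequences are three primary rows against two in the text, and no specified primary test of the proportion suppressed. The fall in power from 75.9% to 70.9% assumes Bonferroni and the planning rates for linkage to care; Hochberg would lose no more. The 10-to-3-point dilution and the 6-point spurious gain rest on assumed rates and on the either/or reading. They show direction and possible scale and are not estimates for this trial. Because these are primary definitions, they should be settled before outcomes are analysed.

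**What to change.** Revise Table 1 to agree with Overview and Primary Outcomes:

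1. Define primary viral suppression as binary, from viral load alone, at a threshold the trial states as its own. The <200 c/mL of the MCC comparison program is one example. Analyse it by logistic or repeated-measures logistic models, which fit the existing analytic approach. List log10 viral load and CD4 count as secondary.
2. Make medication adherence alone the primary adherence outcome, and list appointment attendance as a separate secondary outcome.
3. Move technology use from the primary block to process or engagement measures.

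The change is to wording and analysis specification; no new data are needed. The costs are that continuous viral load and CD4 count lose primary status, a binary outcome discards some information, and some participants may have no chart viral load near the analysis time point. The planned handling of missing data would have to cover that last group.
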